4.4 Recruitment

Patients will be recruited from nine dental hospitals from northern, southern, western and eastern China. The study will be staffed with a clinical research team, who will inform potential participants about the aims, methods and potential risks and benefits of this study. All the investigators from the nine centers will be trained prior to the initiation of the study. Participants will be informed that their participation is voluntary and that choosing not to participate or withdraw will not affect their care. Patients unable to understand or follow the study procedures will not be enrolled. Potential participants will be recruited to the study following signing the written informed consent including information about the trial.

**5. Index of efficacy**

All subjects involved were assigned to treatment group receiving 10mg miconazole mucoadhesive tablet for topical use once a day or control group receiving itroconazole capsule 100mg QD for a treatment period of 2 weeks and followed up for 2 week. Primary outcome measures include the evaluation of clinical symptoms (pain and burning sensation rating), signs (pseudomenbran and erythema grade) candida elimination rate. Secondary outcome measures include ameliorative rate of symptoms, occurrence of adverse events and total usage of other therapies as recorded in the participants’ daily diary and laboratory studies which include blood pressure, electrocardiography, full blood count and liver and kidney function tests.

5.1 Primary outcome measurements

Clinical cure (short and long term): clinical symptoms (pain and burning sensation rating), signs (pseudomenbran and erythema grade)

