**Abstract of Research Scheme**

| Research topic | The Efficacy and Safety of Miconazole Nitrate 10mg Mucoadhesive Tablets Verus Itraconazole Capsules in the Treatment of Oral Candidiasis: A randomized, open label, multicenter phase III trial |
| --- | --- |
| Research objectives | To evaluate the Efficacy and Safety of Miconazole Nitrate 10mg Mucoadhesive Tablets in comparison with Itraconazole Capsules |
| Research design | A randomized, open label, multicenter phase III trial |
| Inclusion criteria | The inclusion criteria: 1) age range of 18-70 years; 2) diagnosis of oral candidiasis was established based on clinical manifestation and laboratory testing (smear test and/or fungi culture); 3) negative reaction to pregnancy test in women and willing to take effective method of birth control in the period of trial. |
| Exclusion criteria | The exclusion criteria: 1) systemic fungal infections or chronic mucocutaneous candidiasis; 2) a history of a known allergy or intolerance to miconazole nitrate and/or itraconazole; 3) use of rifampicin, rifabutin, isoniazid, phenobarbital, phenytoin, methylprednisolone, carbamazepine, terfenadine, astemizole or cisapride; 4) history of psychological or other disorder that unable to cooperate; 5) Abnormal liver and kidney function; 6) history of cardiac disorders such as ischemic heart failure; 7) history of hematological diseases; 8) use of systemic or topical antifungal therapy within 2 weeks before study entry; 9) hyposalivation related disease or drug-taking; 13) HIV infection; 14) history of participating other clinical trials within 4 weeks before study entry. |
| Index of efficacy | Primary: Evaluation of clinical symptoms (pain and burning sensation rating), signs (pseudomembrane and erythema grade).  Scondary: Mycological eradication of organism (by smear test and fungi culture) |
| Index of Safety | Bood pressure, electrocardiography, full blood count and liver and kidney function |
| Dosage regimen | Miconazole Nitrate 10mg Mucoadhesive Tablets Itraconazole 100mg Capsules |
| Course of treatment | 2 weeks treatment and 2 weeks follow-up |

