3.2 Sample size

In the present data of studies on the efficacy of itroconazole treating oral candidiasis, an 85% efficacy rate was assumed. To achieve 80% power with a significance level of 10%(α level, 5%; βlevel, 20%; both 1-sided), 158 participants per group would be required. To compensate for a potential 20% dropout rate, a sample size of 380 participants in total will be applied for this study.

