5.2 Secondary outcome measurements

• Clinical improvement rate: (score of symptom and clinical sign at baseline- score of symptom and clinical sign post treatment)/ score of symptom and clinical sign at baseline

• Mycological: Eradication of organism (negative culture and negative microscopy)*

• Safety: Number of patient withdrawals due to adverse reactions; Incidence of adverse reactions (reported as side-effects).

*Candida albicans is found routinely in asymptomatic population, therefore, it would have been inappropriate to use mycological eradication as the primary outcome measure for the study.

The cure is defined as complete clinical response and eradication of Candida spp. at Day 7 or Day 14. A complete clinical response was defined as the complete disappearance of oral candidiasis lesions, and a partial clinical response was defined as ≥60% of clinical improvement rate compared with the score at baseline. <60% of clinical improvement rate and candida persistence, re-infection or species shifts were considered failures. Finally, biologic, local, and general safety was compared between treatments.

Participants will also be required to complete their daily diaries from the start of the treatment period until the end of the treatment period. Blood tests for full blood count and liver and kidney function tests will be conducted at initial assessment and during the final clinic visit (week 4).

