**11. Statistical Analysis**

11.1 Analysis set

Full analysis set (FAS): it refers to the data set of all subjects participating in

randomization and being evaluated after medication at least once. For those subjects who fail to observe all healing effect evaluation, we conduct the data transfer according to LOCF (last observation carry forward) principle.

Per protocol set (PPS): it refers to the data set of all subjects meeting inclusion criteria, inconsistent with exclusion criteria and completing therapeutic scheme. Analysis (per protocol, PP) is taken on data of all cases consistent with research scheme, with good dependency and completion of filling in contents specified by CRF.

Safety set (SS): It refers to the data set of subjects who are grouped at random, take the research drug and at least have one safety assessment after the baseline.

Baseline comparative analysis and curative effect analysis are conducted based on

FAS and PPS, and safety evaluation is conducted according to SS.

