11.2 Statistical analysis method

Analysis and reporting of the results will follow the CONSORT guidelines for reporting randomised controlled trials. All participants who had at least 1 efficacy evaluation after randomization will be included in the analysis. Safety analyses included all patients who received at least 1 dose of study medication. The trial data will be processed and analyzed by an independent statistician, who will be blinded to participant allocation.

A non-inferiority statistical approach was used. Continuous data were compared using either the Student t test or the Mann-Whitney nonparametric test. For binary data, the 2 treatment groups were compared using the chi-square test or the Fisher exact test. The Mantel-Haenszel test was used to evaluate ordinal quantitative data.

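### Section 3.2 supports 5% alpha and 80% power for one contrast only, while the protocol names clinical cure as primary at two unranked terms and contradicts itself on candida elimination

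*Protocol*

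**What the plan says.** The protocol describes its primary outcome in several places, and they do not agree.

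- Section 5.1 (Primary outcome measurements): "Clinical cure (short and long term): clinical symptoms (pain and burning sensation rating), signs (pseudomenbran and erythema grade". Two terms are named. Neither is ranked or tied to a visit.
- Section 5 (Index of efficacy): "Primary outcome measures include the evaluation of clinical symptoms (pain and burning sensation rating), signs (pseudomenbran and erythema grade) candida elimination rate". Candida elimination is in the primary list.
- Abstract of Research Scheme: "Primary: Evaluation of clinical symptoms (pain and burning sensation rating), signs (pseudomembrane and erythema grade". Mycological eradication is listed there as secondary.
- Section 5.2 (Secondary outcome measurements) also lists eradication as secondary and says that "it would have been inappropriate to use mycological eradication as the primary outcome measure for the study". The same section then makes eradication part of cure and dates it: "The cure is defined as complete clinical response and eradication of Candida spp. at Day 7 or Day 14".

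The sizing in section 3.2 assumes an 85% efficacy rate, without naming an endpoint or visit, and continues: "To achieve 80% power with a significance level of 10%(α level, 5%; βlevel, 20%; both 1-sided), 158 participants per group would be required". On analysis, section 11.2 says "A non-inferiority statistical approach was used" and lists generic tests. It does not say which comparison decides the trial.

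**The concern.** One alpha and one power are attached to a primary set with at least two members. End of treatment (visit 3) and the follow-up two weeks later (visit 4) can give different answers. Miconazole could be non-inferior at one visit and not at the other, and either result could then be presented as the primary one. Section 3.4 leaves participants, investigators and outcome assessors unblinded, so fixing the deciding comparison in advance is an important protection here.

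What the trial's error rates are depends on a success rule that the protocol does not give. If success at either term suffices, the chance of a false non-inferiority claim rises above 5%. If success at both is needed, power falls below the 80% planned with 158 per group.

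**Working it through.** **Inputs.** From section 3.2: 85% efficacy, one-sided alpha 5%, power 80%, 158 per group, 20% dropout, 380 in total. Assumed, because the protocol does not give them: 85% in both arms, a 10-point margin, and the correlation between the test statistics at the two terms. Short and long term are taken as visits 3 and 4 of section 8.3.

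**Step 1: reproduce the plan's figure.** For one binary non-inferiority comparison,

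n per group = (z for alpha + z for power)² × 2 × p(1 − p) / margin²
= (1.645 + 0.842)² × 2 × 0.85 × 0.15 / 0.10² = 157.7, so 158.

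A 9-point margin gives 195 and an 11-point margin 131. With 10 points, one-sided 2.5% gives 201 and one-sided 10% gives 115. The stated 158 therefore fits a single contrast at one-sided 5%. The total follows as 316 × 1.2 = 379.2, so 380, or 190 per arm.

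**Step 2: success at either term counts, each tested at one-sided 5%.** With the true difference at the margin at both terms, the error rate is 1 − P(Z1 < 1.645 and Z2 < 1.645). With independent tests this is 1 − 0.95² = 9.75%.

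**Step 3: success at both terms is required.** Alpha stays at or below 5%. Joint power, with 80% for each test, is the bivariate normal probability that both succeed. With independent tests it is 0.80² = 64%.

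| Correlation | Error rate, either counts | Power, both required (158 per group) |
| --- | --- | --- |
| 0 | 9.75% | 64% |
| 0.3 | 9.3% | 67% |
| 0.5 | 8.8% | 69% |
| 0.7 | 8.0% | 71% |
| 0.8 | 7.5% | 73% |

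**Step 4: rules that keep the stated rates at 158 per group.**
- One named contrast, or the first step of a fixed sequence: 5% and 80% both hold, as in step 1.
- Bonferroni at 2.5% each, with success on at least one: alpha is held at 5%. Power for at least one success is 84% at correlation 0.5, 81% at 0.7 and 79% at 0.8. Power for each single test is 70%.

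**Step 5: all 190 per arm analysed.** Single-test power is 86%. Power with both required is 77% at correlation 0.5 and 80.5% at 0.8.

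**The case against.** The strongest objection is that test order, alpha allocation and the deciding analysis set are commonly left to a statistical analysis plan. One may exist here and is not shown, so the mere absence of a multiplicity rule is not a fault. That is right, and the point does not rest on it. It rests on what the protocol itself states: two unranked primary terms, candida elimination primary in one section and secondary in two other places, a cure definition with no long-term time point, and one sizing calculation. An analysis plan could choose among these, but the protocol sections would still conflict.

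Three stronger readings are tempting, and the documents do not support them.

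- A reader might infer that 5% and 80% cannot both hold. They can. Step 4 shows rules that keep 5% with about 80% or more at 158 per group. If nearly all randomised patients enter the full analysis set, which carries the last observation forward, the power loss from requiring both visits is smaller (step 5).
- A reader might count pain, burning, pseudomembrane, erythema and candida elimination as five separate tests. Section 5.1 can be read as listing symptoms and signs as the content of one endpoint. No section sets a separate non-inferiority test for each score, and section 3.2 sizes a rate, not a rating.
- A reader might treat the two analysis sets as extra chances to succeed, because section 11.1 says "Baseline comparative analysis and curative effect analysis are conducted based on" both the full analysis set and the per protocol set. Nothing there says that success in one set is enough, so no inflation can be charged to it.

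**Conclusion.** The concern holds in a limited form. The stated one-sided 5% and 80% are supported for one binary non-inferiority contrast and are not assured for the primary set as written. With two terms, the false non-inferiority rate is about 8.8% if either counts (9.3% to 7.5% for correlation 0.3 to 0.8). Power is about 69% if both are required and 158 per group are analysed (67% to 73% over the same range). Only one of the two rates is affected under each rule.

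These sizes rest on the inferred 10-point margin, 85% in both arms, the assumed correlations and, for the error rate, a true difference at the margin at both terms. The contradiction over candida elimination and the missing time point for long-term cure need no assumption, because they stand in the text.

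**What to change.** - In sections 5.1 and 11.2, name the between-group difference in clinical cure at one visit, for example visit 3, as the single deciding contrast. In section 3.2, state that the 85% rate refers to that endpoint and visit. At present it is tied to none, so the sponsor has to confirm the match.
- Test clinical cure at visit 4 second in a fixed sequence at one-sided 5%, and only if the first test succeeds. Bring the timing of cure in section 5.2 into line with the two visits, and reconcile it with section 5.1 on whether eradication is part of cure.
- In section 5, make candida elimination and the separate symptom and sign scores secondary, in line with the abstract and section 5.2 on eradication.
- If the sponsor wants success at both visits to be required, keep alpha at 5% and restate the power in section 3.2 as about 69% (67% to 73%) for 158 per group analysed.

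The cost is wording in the protocol, carried into any analysis plan. The downside is that a long-term claim becomes available only after success at the first visit.

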5.2 Secondary outcome measurements

• Clinical improvement rate: (score of symptom and clinical sign at baseline- score of symptom and clinical sign post treatment)/ score of symptom and clinical sign at baseline

• Mycological: Eradication of organism (negative culture and negative microscopy)*

• Safety: Number of patient withdrawals due to adverse reactions; Incidence of adverse reactions (reported as side-effects).

*Candida albicans is found routinely in asymptomatic population, therefore, it would have been inappropriate to use mycological eradication as the primary outcome measure for the study.

The cure is defined as complete clinical response and eradication of Candida spp. at Day 7 or Day 14. A complete clinical response was defined as the complete disappearance of oral candidiasis lesions, and a partial clinical response was defined as ≥60% of clinical improvement rate compared with the score at baseline. <60% of clinical improvement rate and candida persistence, re-infection or species shifts were considered failures. Finally, biologic, local, and general safety was compared between treatments.

Participants will also be required to complete their daily diaries from the start of the treatment period until the end of the treatment period. Blood tests for full blood count and liver and kidney function tests will be conducted at initial assessment and during the final clinic visit (week 4).

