3.4 Blinding level

In this open label study, participants, investigators and outcome assessors will not remain blinded to the treatment.

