**9. Observation of Adverse Event**

9.1 Definition

(1) Adverse event (AE): any unfavorable medical incident happens since the time when the subject signs the informed consent and enrolls the trial to the finish of the last follow-up is judged as adverse event, no matter whether the medical incident is associated with the investigational drug or not.

(2) Significant adverse event: besides severe adverse event, any adverse event happens and causes the use of pointed medical measures (e.g. drug withdrawal, reducing dosage and expectant treatment) and hematological and/or other laboratorial anomaly.

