9.3 Judging standard of the relation between adverse events and investigational drug

The causality analysis of the relation between all adverse events and the investigational drug is judged according to five grades, i.e. certainly related, probably related, possibly related, possibly unrelated and definitely unrelated. The first three grades are judged drug adverse reaction. In the causality analysis we consider the following five aspects.

1) Do the time of beginning to use the medicine and the time of appearance of Adverse Drug Reaction (ADR) have reasonable precedence relation (appearance during using medicine)?

2) Does the suspected ADR match the already-known ADR of the drug (conformity with the literature)?

3) Can the suspected ADR be explained by influences of combining with drug, original drug, clinical state of patients or the effect of other therapies (other explanations)?

4) Do the suspicious ADR disappear or reduce after drug withdrawal or decrement (withdrawal symptom)?

5) Does suspicious ADR appear again after taking the same medicine (taking again, appearing again)?

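### Sections 5 and 5.2 name different safety outcomes, and the one in 5.2 rests on an open-label causality judgement that can differ between arms

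*Protocol*

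**What the plan says.** The protocol describes the safety outcome in several places, and the descriptions differ.

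- **Section 5:** "Secondary outcome measures include ameliorative rate of symptoms, occurrence of adverse events and total usage of other therapies", followed by vital-sign and laboratory measures. The count here is of adverse events.
- **Section 5.2:** the safety item has two parts, "Number of patient withdrawals due to adverse reactions" and "Incidence of adverse reactions (reported as side-effects". Adverse events as such are not listed. A later sentence adds, in general terms, that biologic, local and general safety is compared between treatments.
- **Abstract:** the safety index names only blood pressure, ECG, blood count and liver and kidney function, and neither events nor reactions.

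The two terms are defined separately. Section 9.1 counts an adverse event from consent and enrolment to the end of the last follow-up, "no matter whether the medical incident is associated with the investigational drug or not". Section 9.3 grades causality on five levels and states: "The first three grades are judged drug adverse reaction". One of its five considerations is: "Does the suspected ADR match the already-known ADR of the drug".

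On blinding, section 3.4 says that "participants, investigators and outcome assessors will not remain blinded to the treatment".

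**The concern.** Two teams working from the same case report forms, one following section 5 and the other 5.2, would report different safety figures for each arm, and possibly a different contrast between arms. Comparative safety is a stated objective in section 2, so the choice of count matters.

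The 5.2 count is also the more fragile of the two in this design. Whether an event becomes a reaction depends on a judgement made with the treatment known. One criterion can be applied only by knowing which drug was taken, so the same symptom can count in one arm and not in the other. A difference in tolerability, or the masking of one, could then come from attribution and not from harm. The blinded statistician in 11.2 does not protect against this, because grading is done before the data reach the analysis.

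**Working it through.** The plan gives no adverse event rate, attribution rate or safety power figure, so there is no stated number to reproduce. The main check is a comparison of the text.

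**Step 1: are the two outcomes the same quantity?** Let E be the proportion of patients in an arm with an adverse event (9.1) and a the fraction of those patients whose event receives one of the first three causality grades (9.3). Section 5 reports E. Section 5.2 reports R = E × a. They agree only if a = 1, that is, if no patient's events are all graded in the lowest two levels. The outcomes therefore differ by definition.

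**Step 2: can a differ between arms without a difference in harm?** Section 3.4 leaves participants, investigators and assessors unblinded. Section 9.3 includes the known-reaction criterion and provides for no blinded or independent causality review. Nothing in the document forces a to be equal in the two arms. Withdrawals due to adverse reactions depend on the same judgement.

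**Step 3: how much could it matter?** This is an illustration on assumptions and not an estimate for this trial. Take n = 190 per arm (380 in section 3.2, divided by 2, with everyone in the safety set), the same true E in both arms, and a two-sided 5% test. With p1 = E × a1, p2 = E × a2 and p̄ their mean, the chance of a significant result in the direction of the attribution gap is

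Φ{ [ |p2 − p1| − 1.96 √(2p̄(1 − p̄)/n) ] / √([p1(1 − p1) + p2(1 − p2)]/n) }.

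Worked case with E = 20%, a1 = 50%, a2 = 70%:

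- p1 = 0.20 × 0.50 = 0.10; p2 = 0.20 × 0.70 = 0.14; p̄ = 0.12.
- Null standard error = √(2 × 0.12 × 0.88/190) = 0.0333; alternative standard error = √((0.0900 + 0.1204)/190) = 0.0333.
- Φ{(0.04 − 1.96 × 0.0333)/0.0333} = Φ(−0.76) = 0.22.

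| True event rate, both arms | Attributed 50% v 60% | Attributed 50% v 70% | Attributed 40% v 70% |
| --- | --- | --- | --- |
| 10% | 5% v 6%: 0.06 | 5% v 7%: 0.13 | 4% v 7%: 0.25 |
| 20% | 10% v 12%: 0.09 | 10% v 14%: 0.22 | 8% v 14%: 0.46 |
| 30% | 15% v 18%: 0.12 | 15% v 21%: 0.33 | 12% v 21%: 0.66 |

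Each cell gives the recorded reaction rates and the chance of a spurious significant result in that direction. With equal attribution that chance is 0.025. Exchanging the arms gives the same chances with the opposite sign, so the table says nothing about which drug would look worse.

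**Step 4: is the all-cause count still obtainable?** Yes. Section 9.2 has all clinical adverse events recorded on the case report form, 5.3 has them recorded at each visit, and 9.1 defines them regardless of cause.

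**The case against.** The strongest reply is that this is loose terminology and not a changed endpoint. The protocol mixes the terms elsewhere: 9.4 and 9.5 refer to adverse drug reaction records and forms when discussing adverse events. The parenthesis in 5.2 about side-effects could mean patient-reported complaints and not events graded under 9.3. Section 5 keeps adverse events as an outcome, nothing gives 5.2 precedence over it, and 5.2 itself mentions a broader safety comparison. All events are recorded, so an all-cause table can be produced, and the choice of leading safety table is often left to the SAP.

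Much of this is fair and limits the point. No data would be lost, and the intention behind 5.2 is uncertain. It does not remove the contradiction, because the protocol has itself named the outcome twice and differently, using terms it defines separately. If the side-effects are patient-reported, participants are unblinded too.

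A reader might go further in two ways that the documents do not support.

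- **Bias against the systemic comparator.** No section gives a known-reaction profile or an expected attribution rate for either drug, and the 9.3 criterion is worded alike for both. Local mouth symptoms could as easily be attributed to a tablet fixed to the gum.
- **Attribution by unblinded investigators, as a stated fact.** Section 9.3 names no grader. Site investigators are the likely graders, since 9.4 has them judge abnormal laboratory results, but this is an inference.

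**Conclusion.** The point stands as an internal contradiction with a bias risk attached. Sections 5 and 5.2 name different safety outcomes, and the 5.2 version depends on causality grading in a trial where nobody at the site is blinded and no independent grading is provided. The direction and size of any differential attribution cannot be established from the protocol. The chances of 6% to 66% in the table rest wholly on assumed event and attribution rates, on equal arms of 190 and on full inclusion in the safety set. They show that the risk can be material, not that it is present. The consequence is confined to a secondary, safety comparison; the efficacy analysis is untouched. The protocol states no superiority hypothesis for tolerability, so the harm would come in how a between-arm difference in reactions is interpreted.

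**What to change.** Reconcile sections 5 and 5.2, and bring the abstract's safety index into line.

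- Name the incidence of all-cause adverse events, as defined and timed in 9.1, and withdrawals due to any adverse event as the between-arm safety comparison on the safety set of 11.1.
- Keep adverse reactions under 9.3, and withdrawals due to them, as a supportive table. State who grades causality and that the grading is done with treatment known.

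The cost is a change of wording and one more table; no new data are collected. The change does not remove all open-label bias, because unblinded participants still decide what to report and enter in their diaries. It does take the causality judgement out of the main comparison.

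### The primary outcome is stated inconsistently: candida elimination is both primary and secondary, and clinical cure has no criterion or time point of its own

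*Protocol*

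**What the plan says.** The protocol describes its efficacy outcomes in four places.

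- **Abstract of Research Scheme.** The primary index is symptoms and signs. The secondary index is "Mycological eradication of organism (by smear test and fungi culture").
- **Section 5.** "Primary outcome measures include the evaluation of clinical symptoms (pain and burning sensation rating), signs (pseudomenbran and erythema grade) candida elimination rate". The next sentence, on secondary measures, does not mention mycology.
- **Section 5.1.** The primary outcome is "Clinical cure (short and long term): clinical symptoms (pain and burning sensation rating), signs (pseudomenbran and erythema grade"). No score or threshold marks a patient as cured.
- **Section 5.2.** Among the secondary outcomes is "Mycological: Eradication of organism (negative culture and negative microscopy"). The footnote points to routine carriage of Candida albicans in people without symptoms and concludes that "it would have been inappropriate to use mycological eradication as the primary outcome measure for the study". The text then says "The cure is defined as complete clinical response and eradication of Candida spp", assessed at day 7 or day 14. A complete clinical response is the disappearance of lesions, and a partial response is an improvement rate of at least 60%. Finally, "<60% of clinical improvement rate and candida persistence, re-infection or species shifts were considered failures".

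Section 3.2 assumes an 85% efficacy rate for itraconazole and does not say which endpoint that rate measures. Section 11.2 states a non-inferiority approach. No margin appears anywhere in the protocol.

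**The concern.** A non-inferiority conclusion rests on one comparison of one primary endpoint. Here the sections disagree on whether candida elimination belongs to it. The outcome that 5.1 does name, clinical cure, cannot be scored from the text without borrowing a rule from 5.2 that brings eradication in. Depending on the section applied, the primary success rate could be a clinical rate, a mycological rate or a composite of the two.

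The trial is open label with unblinded outcome assessors (section 3.4), so an endpoint left open can be settled after results begin to show. The sample size is also affected, because the 85% is attached to none of the candidate definitions.

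**Working it through.** **1. Is candida elimination primary?**

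| Place | Mycology |
| --- | --- |
| Abstract | secondary |
| Section 5 | in the primary list |
| Section 5.1 | absent from the primary outcome |
| Section 5.2, list | secondary |
| Section 5.2, footnote | unsuitable as primary |

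Section 5 stands alone against the others. A comma or conjunction seems to be missing before its last item, but restoring one leaves the item in the primary sentence.

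**2. What counts as cured?** Section 5.1 gives components and no threshold. The one criterion in the protocol is the composite in 5.2 (complete clinical response plus eradication), and the text does not say whether it applies to the primary outcome of 5.1 or to a separate secondary outcome.

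**3. Are the response classes coherent?** Complete response looks at lesions only. The improvement rate in 5.2 uses symptom and sign scores together, and 5.1 also counts pain and burning. A patient whose lesions have gone but whose pain persists could be a complete responder and still show less than 60% improvement. The failure sentence joins low improvement and candida persistence with an *and*. It can mean that both are required or that either suffices.

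**4. When is it assessed?** Section 5.1 says short and long term. Section 5.2 sets cure at day 7 or day 14 and gives no follow-up time point, although visit 4 (section 8.3) repeats the clinical and laboratory examination two weeks after treatment stops.

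**5. Does the sample size show which endpoint was meant?** Inputs from section 3.2: 85% efficacy, one-sided α 5%, power 80%, 158 per group, 380 in total. Assumptions: equal true rates and a 10-point margin.

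n = 2p(1−p)(z₀.₉₅ + z₀.₈₀)² / margin² = 2 × 0.85 × 0.15 × (1.645 + 0.842)² / 0.10² = 157.7, so 158 per group.

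This reproduces the plan's figure. Margins of 9 and 11 points give 195 and 131, so 10 points is the likely value, but it is inferred. The arithmetic is the same whichever endpoint the 85% describes, so it does not resolve the conflict.

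**6. Illustration of what depends on the choice.** Power = Φ(0.10 / √(2p(1−p)/n) − 1.645).

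Suppose the 85% is a clinical rate and 20–40% of clinically cured patients still carry Candida (an assumption; the protocol gives no such figure). The composite rate is then 0.85 × 0.60 = 0.51 to 0.85 × 0.80 = 0.68.

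| True rate in both arms | n = 158 per arm | n = 190 per arm |
| --- | --- | --- |
| 0.85 | 80% | 86% |
| 0.68 | 60% | 67% |
| 0.51 | 55% | 62% |

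The 190 column (380/2) is the upper bound, with every randomized patient in the full analysis set. In the other direction, if 85% is the composite rate, clinical cure must be at least as frequent. At 90%, for example, 158 per arm gives Φ(0.10/0.0338 − 1.645) = 91%.

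**The case against.** The strongest reply concerns 5.2. Its footnote rejects eradication as *the* primary measure, which does not logically bar a composite that contains it. The cure definition also sits under the secondary heading, while 5.1 uses the different term clinical cure. So 5.2 may be defining a separate overall cure. That reply stands: a reader might infer that the primary outcome requires eradication, and the documents do not establish this. What remains is that clinical cure then has no criterion at all, and section 5 still conflicts with the abstract and 5.2.

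A reader might also take a patient with cleared lesions and a positive culture and say that the text makes this patient at once a clinical cure, at least a partial responder and a failure. That does not follow. Section 5.1 and the improvement rate also count pain and burning, 5.1 sets no threshold, and the failure label depends on how the *and* is read.

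Nor do the documents show that the trial is under-powered. The lower power figures need a margin that the protocol does not state, a carriage rate that it does not give, an 85% that is a clinical rate, and the composite analysed as primary. The full analysis set, with last observation carried forward, may also hold up to 190 per arm rather than 158.

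Finally, section 11.2 provides an independent statistician blinded to allocation. This limits the scope for a results-driven choice, but it does not say which definition is to be analysed.

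**Conclusion.** The inconsistency is real and rests on the wording alone. Section 5 makes candida elimination primary against the abstract, 5.1 and 5.2. Clinical cure has no criterion, and the only cure rule available includes eradication without being tied to an outcome. The response classes and the assessment times do not fit together. In a phase III non-inferiority trial this needs correcting, because the primary conclusion depends on it.

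The numerical consequence is illustrative and can go either way. Under the assumed 10-point margin and a 51–68% composite rate, power is about 55–60% at 158 per arm and 62–67% at 190 per arm. It is above 80% for clinical cure if the 85% is itself a composite rate.

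**What to change.** 1. **Section 5:** delete candida elimination rate from the primary measures.
2. **Section 5.1:** make clinical cure the single primary outcome, with one explicit criterion built on the symptom and sign scores already collected, and one primary time point. All scores equal to zero is one possible criterion. It is a proposal, since no section implies a threshold. The remaining time point can be secondary.
3. **Section 5.2:** rename the composite overall (clinical plus mycological) cure, keep it secondary, and align its timing with 5.1.
4. **Section 5.2:** make the clinical response classes mutually exclusive and base them on the same scores. Tabulate persistence, re-infection and species shift separately, so that the ambiguous failure sentence is no longer needed.
5. **Section 3.2:** check in the source of the 85% which endpoint it describes, and say so. If it is not the chosen primary outcome, revisit the sample size. The 85% should not simply be declared to fit.

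The cost is wording in sections 3.2, 5, 5.1 and 5.2, plus one check of a source. No extra visits or measurements are needed, because smear, culture, symptom and sign data are already scheduled in section 8.3. Any change to the sample size would depend on item 5.
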